**Fig. 1 Fig1:**
[figure not shown]
Study flow chart

### Outcome measurements and follow-ups

#### Primary outcome measure

The primary outcome measure is the change in the THI score [20]. The THI is a self-administered test including 25 questions that determine the degree of function, emotional status, and adverse reactions in the patient with tinnitus. The respondent answers the questions on a 3-point Likert scale with responses of “no” (0 points), “sometimes” (2 points), and “yes” (4 points) yielding an overall score ranging from 0 to 100. The following criteria are used to determine effectiveness [21]: curative = THI score decreased to less than 16 points; significantly effective = THI score decreased by more than 17 points; and ineffective = THI score decreased by less than 17 points, or even increased. The THI has been demonstrated to be a well-known, reliable, and valid clinical tool when evaluating the severity of tinnitus and for assessing the performance of HAs [22]. The proposed study will use the THI Chinese (Mandarin) version [23].

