**Methods and design:**

The present study is a prospective, single-center, outcome assessor and data analyst-blinded, randomized, controlled trial. Eligible participants will be recruited and randomly allocated into the HA intervention group and the waiting list control group at a ratio of 1:1. The primary outcome is to evaluate the severity of tinnitus using the Tinnitus Handicap Inventory as a continuous variable at 6 months from randomization. Secondary outcome measures include changes in hearing status and mental states. The trial will last 6 months, with follow-up visits at 3 months and 6 months.

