### Recruitments and randomization

This study will be conducted in the outpatient ENT department of the Eye and ENT Hospital of Fudan University in Shanghai, China. Our institution is a specialized hospital focused on otorhinolaryngology. In addition, we developed an app—the Fudan Tinnitus Relieving System (FTRS)—that will be used for the management, treatment, data collection, and efficacy analysis of tinnitus patients. The participants will be primarily included in the study after being diagnosed with probable chronic subjective tinnitus with bothersome symptoms after the screening procedure. Screening for hearing and tinnitus testing typically consists of PTA, speech audiometry test, and distortion product otoacoustic emissions (DPOAE) along with several widely accepted tinnitus questionnaires such as the THI for tinnitus severity, the visual analog scale (VAS) for tinnitus loudness, and the HADS and AIS-8 for mental health status. The entire test will generally take a mean time of approximately 30 min. Participants will scan the two-dimensional code we supply via their smartphones and will fill out the questionnaires online through the FTRS.

Interested patients will be directed to the research room to receive the necessary details of the study. Before participation, informed and written consent will be obtained from all participants by the principal investigator. The randomization will be stratified by the THI score (≤ 36 or > 36 [18]) based on the baseline assessment in order to avoid an uneven distribution of patients. An independent researcher who is not involved in the recruitment process or outcome measurement will generate a random sequence (http://www.random.org) to randomly assign the participants in a 1:1 allocation to treatment using HAs or to the WLC group. The randomization sequence will be concealed in sequentially numbered sealed and opaque envelopes. Participants will then be notified via telephone or email which group they are allocated to by the staff member who kept the randomization sequence file and who will not participate in any subsequent assessment of the patients. Data analysts, study coordinators, and outcome assessors will remain unaware of the group assignments until the primary analyses are completed.

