### Sample size, data collection, and statistical methods

The calculations will be analyzed by the PASS Power Analysis Software (NCSS; Kaysville, UT, USA). According to the power calculations, we assume an *α* of 0.05 and a power of 0.8. The sample size estimation was calculated by the PASS software using the Test for Two Proportions. Based on our clinical experience, feasibility, and the previously reported study [33], with the incidence of a 20% improvement in THI set to 75%, the calculated sample size is 56 participants with a 1:1 allocation. The lost-to-follow-up rate is estimated to be 10%, so we plan to enroll 31 participants in each group.

The data collection will use the FTRS collection platform and the hospital information system to record the answers to the questionnaires and the outcomes of the clinical testing. The questionnaires are designed with inbuilt check-and-skip rules after pretesting by study staff to minimize data-entry errors. The data will be centralized, classified, and protected in long-term storage in the data repository.

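### The THI effectiveness categories are not mutually exclusive, and the sample size is planned on a responder rule that matches none of them

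*Protocol article*

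**What the plan says.** All references are to the protocol article.

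- **Primary outcome measure.** "The primary outcome measure is the change in the THI score". The scale has 25 items scored 0, 2 or 4, "yielding an overall score ranging from 0 to 100". Effectiveness is then graded. Two grades are successes: "curative = THI score decreased to less than 16 points; significantly effective = THI score decreased by more than 17 points". The third grade covers failures and is again a rule on the change: "ineffective = THI score decreased by less than 17 points, or even increased". No precedence among the three grades is stated.
- **Abstract, Methods and design.** The primary outcome is the "Tinnitus Handicap Inventory as a continuous variable at 6 months from randomization".
- **Participants; Recruitments and randomization.** The eligibility list has no minimum THI. "The randomization will be stratified by the THI score", with strata of 36 or less and more than 36.
- **Sample size, data collection, and statistical methods.** A two-proportion test is used, "with the incidence of a 20% improvement in THI set to 75%, the calculated sample size is 56 participants with a 1:1 allocation". The same section plans to compare THI scores between groups by t-test and by a linear model adjusted for age, gender and baseline.

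**The concern.** 'Curative' is a rule on the final level, while 'significantly effective' and 'ineffective' are rules on the change. Rules of these two kinds overlap unless an order is given. The overlap that matters puts one patient among both the cures and the failures, so any reported effectiveness rate depends on a coding decision that the article does not make.

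The responder definition behind the sample size is different again. The 75% therefore cannot be set against any category that the trial has defined, and a reader of the results could not tell whether the planning assumption was met.

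**Working it through.** **Inputs.** Items score 0, 2 or 4, so totals are the even numbers 0 to 100 and every fall is even. Write *b* for baseline, *f* for final score and *d* = *b* − *f*. 'Curative' is *f* < 16 with *d* > 0, 'significantly effective' is *d* > 17, and 'ineffective' is *d* < 17.

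**1. The plan's own figure.** The total of 56 (28 per group) cannot be reproduced, because only one rate, 75%, is given. Solving backwards with a two-sided test and no continuity correction,

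n = [1.96·√(2p̄q̄) + 0.842·√(p₁q₁ + p₂q₂)]² / (p₁ − p₂)²,

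p₁ = 0.75 and p₂ = 0.385 give (1.373 + 0.548)² / 0.365² = 27.7, so 28. Across one- or two-sided tests, with or without correction, the implied comparator rate runs from about 34% to 43%. Reading the 20% as a difference between arms does not give 28 either: 75% against 55% needs 89 per arm, and 75% against 95% needs 49 (two-sided, uncorrected). One-sided, these become 70 and 39. So the figure does not reveal which responder rule was meant.

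**2. Is there a gap at exactly 17?** No. Falls are 16 or 18, never 17. Every pair of scores falls in at least one category, and the fault is overlap only.

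**3. 'Curative' and 'ineffective' together.** This requires *f* ≤ 14 and 2 ≤ *d* ≤ 16.

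- Baselines 16, 18, …, 30 allow 8, 7, …, 1 final scores: 8 + 7 + … + 1 = 36 pairs.
- Baselines 2, 4, …, 14, read literally, allow 1, 2, …, 7: 1 + 2 + … + 7 = 28 pairs.
- Total 64 pairs. These are combinations of scores, not expected patients.

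'Curative' and 'significantly effective' also coincide, for *f* ≤ 14 and *d* ≥ 18: 42 + 41 + … + 35 = 308 pairs. That overlap is less serious, since both labels are successes.

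**4. The 20% rule against the 17-point rule.** Read as a relative fall, the smallest even fall reaching 20% is 8 points at baseline 36, 10 at 50 and 16 at 80. At baseline 82 it is 18, because 0.20 × 82 = 16.4 and the next even number is 18. So a 20% responder can be 'ineffective' at any non-zero baseline up to 80 (152 pairs). From 82 to 90 the two rules agree. From 92 to 100 an 18-point fall is 'significantly effective' but below 20%. Read instead as a fall of at least 20 points, the rules differ only for a fall of exactly 18.

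| Baseline → final | Fall | Final < 16 | Fall > 17 | Fall < 17 | Relative 20% met |
|---|---|---|---|---|---|
| 28 → 14 | 14 (50%) | yes | no | yes | yes |
| 14 → 12 | 2 (14%) | yes, read literally | no | yes | no |
| 40 → 14 | 26 (65%) | yes | yes | no | yes |
| 50 → 40 | 10 (20%) | no | no | yes | yes |
| 100 → 82 | 18 (18%) | no | yes | no | no |

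**The case against.** The strongest reply is that none of this touches the primary test. The abstract fixes THI as continuous, the outcome section names the change in score, and the statistical methods compare scores. No between-group test of the three categories is specified; a chi-square test is listed, but not for a named variable. This stands, and it sets the limit of the point.

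A reader might go further and infer that the effectiveness rates would reflect the baseline mix rather than treatment, or that coding could be chosen to favour an arm. The document supports neither. Falling by more than 17 points, or to below 16, can plainly depend on treatment, and stratification at THI 36 limits baseline imbalance. Recruitments and randomization and Blinding both keep those who analyse and assess outcomes unaware of allocation until the analyses are done. A late coding choice would be arbitrary, but on the stated plan it could not be steered.

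It can also be said that the best-to-worst listing implies a hierarchy, that the scheme comes from a cited source, and that precedence is a detail for a fuller document. A hierarchy is plausible but not stated, and the criteria are given in full as the means of judging effectiveness. What is printed yields contradictory labels; it is not merely brief. If 'decreased to' means crossing 16 from above, the 28 pairs with baselines 2 to 14 drop out and the 36 with baselines 16 to 30 remain.

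Finally, patients are described as having bothersome symptoms, which might exclude very low scores. That is not tied to a THI value, and the Discussion speaks of mild symptoms.

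**Conclusion.** The point holds as a defect in the effectiveness classification and in the planning rate. At baselines 16 to 30, a final score of 14 or below after a fall of at most 16 points carries two contradictory labels. On a literal reading, so does any fall from baselines 2 to 14. Such patients can be enrolled, because there is no entry minimum and one stratum is THI 36 or less, but the document gives no baseline distribution, so their share of the 62 planned cannot be stated.

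The 75% planning rate belongs to none of the defined categories. The mismatch is wide if 20% is a relative fall (baselines up to 80) and narrow if it means 20 points (an 18-point fall only). The text does not say which. The absent comparator rate is a separate matter.

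The primary continuous comparison is not invalidated. The results rest on even totals, which follow from the item scoring, and on 'curative' requiring some decrease.

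**What to change.** Before unblinding, make the categories mutually exclusive in one of two ways.

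- **One change rule.** Class every randomised patient as effective (fall of more than 17 points) or ineffective (otherwise), and report a final THI below 16 separately as a descriptive level. Patients starting below 18 cannot then be effective, and 30 to 14 counts as ineffective; say so in the report.
- **Explicit precedence.** Let 'curative' come first, but require a baseline of 16 or more. This stays closer to the cited scheme, but a 2-point fall from 16 to 14 would still count as curative.

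Under either, state that the continuous THI difference decides efficacy. In the sample-size text, say whether 20% is relative or in points, and reconcile that responder rule with the outcome section.

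Do not remove low-baseline patients from the summary: that would sit badly with the intention-to-treat statement. At most, show the categories by the existing THI stratum.

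The cost is slight rewording and a small departure from the cited scheme. No new data or visits are needed, and every patient stays in the primary analysis.

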#### Secondary outcome measures

##### SRS

Speech audiometry combines linguistic and acoustic measurements to assess auditory sensitivity and clarity. The SRS test uses a Mandarin monosyllabic word list [24], and participants—who are inside an isolated soundproof chamber—are instructed to repeat each monosyllabic word. The list comprises 25 monosyllabic words, and each word has a score of 4 points on a scale of 100 points such that the scores are given as percentages. A higher score indicates a better level of auditory comprehension and speech recognition.

##### PTA

PTA calculates the average hearing thresholds in decibels (dB) obtained at multiple frequencies. The test is administered in a double-walled soundproof audiometric treatment room with a speaker located 1 m directly in front of the participant. An average hearing threshold above 25 dB at high frequencies (2–8 kHz) is defined as high-frequency SNHL. Participants will be required to undergo PTA at 0.5, 1, 2, and 4 kHz to derive accurate hearing threshold data.

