## Abstract

**Background:**

Chronic subjective tinnitus poses significant challenges in clinical practice, and it is usually associated with hearing impairment, particularly with high-frequency sensorineural hearing loss (SNHL). Patients suffering from tinnitus with SNHL experience one of the most severe sensory disabilities, and this has devastating effects on their quality of life. Nowadays, mild to moderate SNHL can be managed with a properly fitted hearing aid (HA) that provides sound amplification, and several studies suggest that HAs may also benefit those with tinnitus. However, inadequate attention has been paid by medical personnel to the impact of HA use in residual hearing protection for patients with tinnitus and coexisting SNHL, and existing evidence is still at a preliminary stage. This study aims to identify and evaluate the efficacy of the use of HAs in both sound perception and residual hearing preservation among patients with tinnitus and coexisting SNHL.

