Currently, the use of hearing aids (HAs) is widely considered to be an effective instrument for older patients with hearing disabilities. HAs mostly function through sound amplification, and it is noteworthy that the enhanced performance of receiving acoustic information by using HAs is also seen in patients with significant residual hearing [12]. Surprisingly, several studies have shown that HAs might help patients cope with their tinnitus by increasing the external volume to help cover the tinnitus sound [13–16]. However, these previous studies in general do not comprehensively explore the role of HA in the severity or loudness of tinnitus, and there is still little agreement on the relationships between the HA intervention and residual hearing preservation in terms of hearing improvement.

Considering the lack of compelling evidence regarding the extent to which HAs play a role in sound perception and residual hearing preservation among patients with tinnitus and coexisting SNHL, we designed this single-blind, 6-month, randomized, controlled trial with two parallel groups. The first is the HA treatment group, and the second is the waiting list control (WLC) group that will receive non-HA interventions during the study period. We hypothesize that the HA intervention will improve tinnitus patients’ quality of life in terms of improvements in the speech recognition score (SRS), the Tinnitus Handicap Inventory (THI), the Hospital Anxiety and Depression Scale (HADS), and the Athens Insomnia Scale-8 (AIS-8) without affecting residual hearing.

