### Intervention

Following randomization, the participants will be immediately invited to provide personal information including primary demographic data and clinical characteristics. Demographic variables will include gender, age, occupation, residential address, education level, date of onset, and comorbidities. Once participants are randomized and the baseline measurements are complete, the intervention will begin.

Participants in the treatment group are required to wear the HAs for at least 3 h per day and for at least 24 days per month. The HAs will be fitted unilaterally or bilaterally on the side affected by tinnitus, and the HA fitting prescription will be in accordance with the NAL-NL1 procedure [19]. A comfortable and precise level of auditory perception is of the utmost importance in the debugging process of the HA. We will also evaluate the HA performance in the HA treatment group using the Abbreviated Profile of Hearing Aid Benefit (APHAB) questionnaire. The non-HA treatment group is a WLC in which participants will receive the intervention after the waiting period has passed. All participants will receive regular counseling and lifestyle education from physicians during the study period.

The flow chart for participant visits and follow-ups is shown in Fig. 1. To assess the outcome efficacy of HAs, all of the participants will undergo follow-up assessments at 3 months and 6 months after the start of the intervention.

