### Blinding

For this intervention, it is not feasible to blind participants and clinicians regarding the treatment condition owing to the nature of the clinical treatment modalities. However, by separating the intervention and analysis staff, independent investigators in our hospital will perform all follow-up evaluations blinded to the group allocation. We will also attempt to minimize assessment bias and achieve the maximum trial blinding through the following measures: (1) both the data collectors and the assessors will be trained to achieve high interrater reliability, (2) participants and data collectors will be masked as far as possible to block size when collecting the data, and (3) the outcome data assessor will be blinded from randomization until the statistical analyses of the experimental outcomes are completed.

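### PTA through one frontal loudspeaker follows the better ear, so in unilateral fits it can miss a change in the ear that receives the hearing aid

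*Protocol article*

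**What the plan says.** The PTA paragraph under Secondary outcome measures fixes the set-up: "The test is administered in a double-walled soundproof audiometric treatment room with a speaker located 1 m directly in front of the participant". It defines the outcome without naming an ear: "PTA calculates the average hearing thresholds in decibels (dB) obtained at multiple frequencies". It then lists the test frequencies: "Participants will be required to undergo PTA at 0.5, 1, 2, and 4 kHz to derive accurate hearing threshold data". The article mentions no earphones, inserts, masking or plugging, and no other section replaces the loudspeaker with another method.

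The Participants section accepts tinnitus on one or both sides. The Intervention section follows that laterality: "The HAs will be fitted unilaterally or bilaterally on the side affected by tinnitus". Under Time points, PTA is repeated at 3 and 6 months, together with DPOAE and the speech recognition score (SRS).

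Residual hearing is central to the stated purpose. The abstract's aim is to evaluate the "efficacy of the use of HAs in both sound perception and residual hearing preservation among patients with tinnitus and coexisting SNHL", and the hypothesis at the end of the Background is that patients benefit "without affecting residual hearing".

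**The concern.** A loudspeaker in front of the listener reaches both ears, and the listener responds as soon as either ear hears the tone. For a participant fitted on one side, the residual-hearing question concerns the fitted ear, but the recorded threshold belongs to whichever ear is better. If the fitted ear is not the better one, its threshold can worsen while the recorded value stays the same.

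The error has a direction. A real loss in the treated ear tends to read as no change, which is what the no-harm hypothesis predicts. The same insensitivity applies to the tinnitus ear of a control participant with unilateral tinnitus, so a protective effect of the aid would be hidden as well. Either way the comparison is drawn toward no difference, and a null PTA result would be hard to interpret.

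**Working it through.** The plan gives no figure to reproduce here: it states no expected PTA change and no share of unilateral cases. The check is a small model, and every decibel input below is an assumption.

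**Inputs from the protocol article**
- One frontal loudspeaker, no ear named (PTA).
- One or both ears fitted, on the tinnitus side (Intervention).
- Unilateral tinnitus admitted (Participants).

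**Model.** Let F be the threshold of the fitted ear and O that of the other ear. Higher values mean worse hearing. The unaided sound-field threshold is taken as min(F, O), ignoring any summation between the ears. Let a = F − O, and let the fitted ear lose d dB while the other ear is stable. The recorded change is

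min(a + d, 0) − min(a, 0).

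**Step 1: fixed asymmetry, unilateral fit**

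| a (fitted minus other) | d = 5 dB reads as | d = 10 dB reads as |
|---|---|---|
| −10 (fitted ear better) | 5 | 10 |
| −5 (fitted ear better) | 5 | 5 |
| 0 | 0 | 0 |
| 5, 10 or 20 (fitted ear worse) | 0 | 0 |

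For example, with a = −5 and d = 10: min(5, 0) − min(−5, 0) = 0 + 5 = 5 dB. With a = 5 and d = 10: min(15, 0) − min(5, 0) = 0 dB.

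**Step 2: asymmetry varying between participants, unilateral fit.** With a normally distributed, the average share of the loss that is recorded was found by simulation (400,000 draws):

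| Mean of a | SD of a | d = 5 dB | d = 10 dB |
|---|---|---|---|
| 0 | 5 | 32% | 20% |
| 0 | 10 | 40% | 31% |
| 5 | 5 | 7% | 4% |
| 5 | 10 | 23% | 17% |
| 10 | 5 | 1% | 0% |
| 10 | 10 | 11% | 7% |

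**Step 3: bilateral fit.** If both ears lose 10 dB, from equal thresholds or from thresholds 10 dB apart, the better ear also moves by 10 dB and the full 10 dB is recorded.

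**Step 4: effect on an arm mean.** Let u be the share of unilateral fits and c the captured share from Step 2. If bilateral ears shift together, the recorded share of a common loss is u·c + (1 − u) = 1 − u(1 − c). With c between 0 and 0.40, the part missed lies between 0.60u and 1.00u. Since u is not given, this cannot be turned into one number. If u were 0.5, for instance, 30% to 50% of the shift would be missed.

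**The case against.** The best defence is that the defect is confined to a subgroup of unknown size. Steps 1 and 3 bear this out: bilateral fits are tracked, and so, in full or in part, are unilateral fits on the better ear. DPOAE is a second, objective hearing measure at both follow-up visits and does not use the loudspeaker, so the residual-hearing aim does not rest on PTA alone. The primary outcome and the sample size are based on THI and are untouched. All of this stands and limits the point. It does not remove it: DPOAE gives no hearing threshold, and the loudspeaker is a stated method, so the condensed format of an article does not explain it away.

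A reader might go further in four ways that the document does not support.

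- **PTA was done with the aid on.** The article gives no test condition. Aided or unaided is a detail that a full protocol can hold, so its absence here does not show that amplification would be measured as hearing.
- **Assessors would be unblinded.** The Blinding section says that "independent investigators in our hospital will perform all follow-up evaluations blinded to the group allocation". A conflict arises only if aids are worn or visible during testing, which is not stated.
- **Eligibility was read from the wrong ear.** The loudspeaker sentence stands under a secondary outcome. The section on recruitment lists PTA at screening without naming a transducer.
- **SRS shares the fault.** The SRS paragraph mentions a soundproof chamber but no loudspeaker.

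**Conclusion.** The point holds in limited form. As specified, PTA does not isolate the fitted ear. In unilateral fits where that ear is equal to or worse than the other, it can register little or none of a change there, which biases this secondary outcome toward no effect. It would be too strong to say that PTA cannot measure residual hearing in the treated ear, because in bilateral fits, or where the fitted ear is the better one, it does respond.

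The size is illustrative: 0 dB recorded for a 5 or 10 dB loss in an equal or worse fitted ear, and roughly 0% to 40% captured on average over the assumed asymmetries. These figures rest on the better-ear model, on a stable other ear, and on testing without masking or plugging. None of the decibel values comes from the document, and the effect on the arm mean scales with the unreported unilateral share. The change is worth making because residual hearing is in the trial's title, aim and hypothesis. It does not threaten the primary THI analysis.

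**What to change.** Replace the loudspeaker PTA with unaided air-conduction thresholds for each ear, by earphone or insert with masking as needed, at baseline, 3 and 6 months.

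Name the analysed ear: the tinnitus (fitted) ear in the hearing aid arm against the tinnitus ear in the waiting list arm. State in advance how bilateral cases enter the analysis, for example the mean of both ears or a fixed choice of ear. If a sound-field or aided test is also wanted, report it as a separate measure.

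The cost is a change of wording and a few extra minutes per visit with routine equipment. Timing matters, because an ear-specific baseline that is not recorded before fitting cannot be recovered afterwards. If ear-level audiograms are already taken in the clinic, the protocol need only say so and make them the PTA outcome.

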##### DPOAE

The DPOAE test might help determine the mechanism behind tinnitus because it determines whether or not the outer hair cells are overexcited or damaged [25]. DPOAE has the advantage of high-frequency specificity and is an objective and non-invasive measurement for diagnosing hearing impairments [26], which can benefit patients with tinnitus and SNHL.

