### Time points

All of the enrolled patients will undergo a clinical evaluation, sign the consent, and record their basic personal information at the baseline measurement. After the stratified randomization, patients will be informed of their group allocation and will correspondingly receive the intervention over the next 6 months. The follow-up visits will be at 3 months after baseline measurement (*t*_1_, mid-way through the intervention) and at 6 months (*t*_2_, the end of the study). The follow-up assessments will comprise the THI, PTA, SRS, DPOAE, VAS, HADS, and AIS-8, and related questionnaires will be developed and distributed in the FTRS. The schedule of enrollment, interventions, and assessments adhering to the SPIRIT 2013 statement is outlined in Fig. 2.

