## Discussion

SNHL presents an overarching factor and significant confounder in the occurrence and progression of subjective tinnitus. Based on the neuroanatomical studies in tinnitus, it has been shown that the reduced auditory input due to SNHL may lead to neural reorganization and cortex synaptogenesis [37]. Furthermore, most individuals with subjective tinnitus tend to have hearing impairment at high frequencies [38], emphasizing the significance of preserving residual hearing. For auditory comprehension, hair cells in the inner ear are crucial. The hair cells in the apical part of the cochlea detect low-frequency sounds, while those in the basal part detect high-frequency sounds. Because mammalian cochlear hair cells cannot regenerate spontaneously, any damage to the cochlea will have long-term detrimental effects on daily speech and quality of life. Therefore, the protection of residual low-frequency hearing could have significant public health benefits, especially in terms of improved speech understanding [39, 40]. HAs are an efficacious therapy option for patients with hearing impairment, particularly in older patients, and HAs may also benefit patients with tinnitus and SNHL by amplifying the sound and giving partial masking relief.

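### The only PTA frequencies listed (0.5, 1, 2 and 4 kHz) do not cover the 2–8 kHz band that defines entry and high-frequency SNHL

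*Protocol article*

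**What the plan says.** Under Participants, the protocol article requires mild high-frequency SNHL, set as a PTA average of 25–40 dB over 2–8 kHz. The PTA subsection of the secondary outcomes uses the same band: "An average hearing threshold above 25 dB at high frequencies (2–8 kHz) is defined as high-frequency SNHL". The sentence that follows gives the test frequencies: "Participants will be required to undergo PTA at 0.5, 1, 2, and 4 kHz to derive accurate hearing threshold data".

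No other list of PTA frequencies appears. Recruitments and randomization names PTA as a screening test without frequencies. Time points does the same for 3 and 6 months: "The follow-up assessments will comprise the THI, PTA, SRS, DPOAE, VAS, HADS, and AIS-8".

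The Background of the Abstract sets the aim as the "efficacy of the use of HAs in both sound perception and residual hearing preservation among patients with tinnitus and coexisting SNHL". The Discussion argues that "the protection of residual low-frequency hearing could have significant public health benefits". It also hopes to show that the coexisting SNHL can be kept from getting worse, and it counts frequency-specific PTA limits among the strengths of the entry criteria.

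**The concern.** Two consecutive sentences in the PTA subsection do not fit together. One defines the condition by an average up to 8 kHz, and the next lists tones that stop at 4 kHz. Followed as written, the plan cannot form its own 2–8 kHz average as an outcome, and it cannot form it at screening either if the list applies there.

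Hearing preservation is in the trial's title, and PTA is the only outcome that gives hearing thresholds in dB. The Background hypothesises that hearing aids help without affecting residual hearing. A measure that is insensitive in the band where the participants' loss is defined makes that result easier to report. It would equally shrink a true benefit there. An 8 kHz threshold not recorded at baseline cannot be recovered by any later analysis.

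**Working it through.** The article gives no PTA effect size or power figure, so there is none to reproduce. The check compares the frequency sets and then works through the averages.

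**Inputs from the article**
- Entry: average of 25–40 dB over 2–8 kHz (Participants).
- Definition of high-frequency SNHL: average above 25 dB over 2–8 kHz (PTA).
- Listed tones: 0.5, 1, 2 and 4 kHz (PTA).

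**Assumptions, not in the article**
- The 2–8 kHz band is represented by 2, 4 and 8 kHz, equally weighted.
- The PTA outcome is the equally weighted mean of the four listed tones.

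**Step 1: overlap.** {0.5, 1, 2, 4} and {2, 4, 8} share {2, 4}. Two of the four listed tones (0.5 and 1 kHz) lie below the band. 8 kHz is missing, as is 6 kHz if the band average is meant to include it.

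**Step 2: eligibility, if the list applies at screening.** Write t2, t4 and t8 for the thresholds at 2, 4 and 8 kHz. The criterion is 25 ≤ (t2 + t4 + t8)/3 ≤ 40, which gives 75 − t2 − t4 ≤ t8 ≤ 120 − t2 − t4.

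| t2, t4 (dB) | Mean of 2 and 4 kHz (dB) | t8 needed for entry (dB) |
|---|---|---|
| 15, 25 | 20 | 35 to 80 |
| 20, 30 | 25 | 25 to 70 |
| 25, 35 | 30 | 15 to 60 |
| 30, 40 | 35 | 5 to 50 |

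In every row, eligibility depends on a threshold that is not on the list. In the first row the 2 and 4 kHz mean is below 25 dB, yet the patient qualifies if t8 is 35 to 80 dB. If 6 kHz is also in the band average, two unlisted thresholds matter: with 20 and 30 dB at 2 and 4 kHz, the 6 and 8 kHz thresholds must sum to between 4 × 25 − 50 = 50 and 4 × 40 − 50 = 110 dB.

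**Step 3: sensitivity as an outcome.** For a 10 dB loss at the frequencies shown, the change in each average is the sum of the losses at its own tones divided by 4 or by 3.

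| Loss of 10 dB at | Change in 0.5/1/2/4 kHz mean (dB) | Change in 2/4/8 kHz mean (dB) |
|---|---|---|
| 8 kHz only | 0/4 = 0 | 10/3 = 3.3 |
| 4 kHz only | 10/4 = 2.5 | 10/3 = 3.3 |
| 4 and 8 kHz | 10/4 = 2.5 | 20/3 = 6.7 |
| 2, 4 and 8 kHz | 20/4 = 5 | 30/3 = 10 |

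Loss confined above 4 kHz does not register. A uniform shift across the band is halved, because only 2 of the 4 averaged tones lie in it. Both averages are linear, so a between-group difference shrinks by the same factor.

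**The case against.** The other side has several sound points.

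- **The scope of the list is open.** The sentence sits under the secondary outcomes and mentions neither screening nor follow-up. The Discussion's reference to frequency-specific PTA limits fits a fuller screening audiogram, and a condensed article may leave that detail to the full protocol. A reader might infer that no participant's eligibility can be verified. The text supports that only if the list also governs screening.
- **High-frequency loss is not invisible.** A reader might infer that the listed PTA cannot detect it at all. But 2 and 4 kHz lie inside the band and are measured, so loss there is seen, though diluted in a four-tone mean.
- **PTA is not the only hearing outcome.** SRS and DPOAE are both collected at 3 and 6 months, and of the latter the article says "DPOAE has the advantage of high-frequency specificity and is an objective and non-invasive measurement for diagnosing hearing impairments". DPOAE gives no threshold average and its test frequencies are not stated, so it softens the gap without closing it.
- **The low frequencies belong.** The Discussion stresses residual low-frequency hearing, and 0.5 and 1 kHz serve that aim. Measuring them is no error. A single mean across both regions, however, isolates neither.
- **The halving is conditional.** The article describes PTA as an average over several frequencies but does not fix the summary to be analysed. It also states no rule for declaring hearing preserved, so one cannot say that a false claim would follow.

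These points narrow the finding. The mismatch remains: the only listed frequencies do not reach the top of the band that the article itself uses, and neither the screening text nor the follow-up text overrides them.

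**Conclusion.** The concern holds in a limited form. The listed PTA frequencies do not cover the 2–8 kHz band that defines entry and disease, and the Participants and PTA sections must be reconciled.

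- **Certain from the text:** as an outcome, the listed PTA cannot register change above 4 kHz and cannot yield the 2–8 kHz average.
- **Conditional on the list applying at screening:** the entry average cannot be computed.
- **Conditional on an equally weighted four-frequency mean:** a uniform 10 dB shift across 2–8 kHz reads as 5 dB, which leans towards finding no deterioration.

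A reader might go further and doubt the trial's main result. The documents do not support that. PTA is secondary, the primary outcome is the THI, and the sample size does not rest on PTA. The primary analysis is touched only through who is enrolled.

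**What to change.** Reconcile the Participants and PTA sections:

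1. Specify one audiogram for screening, 3 months and 6 months that includes 8 kHz alongside 0.5, 1, 2 and 4 kHz.
2. Name the frequencies that make up the 2–8 kHz average, and use that one definition for eligibility and for a PTA outcome.
3. Report 0.5 and 1 kHz separately, to address the low-frequency residual hearing argued for in the Discussion.

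The cost is a wording change and a few extra tones per ear in a test already scheduled at each of these visits. The primary outcome and the sample size are unchanged. The change is needed before baseline audiograms are taken. For anyone already tested without 8 kHz, the missing baseline should be reported as such.
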